### **Study endpoints**

The primary study outcome is the duration of antibiotic treatment (number in 24-hour periods between start and end of antibiotic treatment) within 14 days of the admittance of included neonates and children in each study arm (superiority analysis). Antibiotic use during admittance and a composite measure of antibiotic use during admittance and discharge are reported. For every participant, the types and quantity of antibiotics given during the study period will be assessed based on individual drug administration records. To ensure patient safety in case of reduction in antibiotic use a second primary outcome relapse of infection is measured as reinstitution of antibiotics within 72 h after completion of the initial course of antibiotic treatment.

The secondary study outcomes are:

1. Antibiotic use (prescribed daily doses)
2. Choice of antibiotic drug and dose compared to local standard treatment guidelines
3. Number of days admitted in hospital
4. Number of days until resolution of symptoms
5. Development of clinical signs of sepsis
6. Proportion of cases with blood cultures collected before antibiotic treatment
7. Bacterial pathogens and AST in blood cultures
8. Hospital re-admittance within 14 days
9. Mortality at follow up day 7 and 28

Our definition of prescribed and defined daily doses accords with the recommendations of WHO. The route of administration will be incorporated in the daily dose calculations.

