## **Methodology**

### **Study design**

This study is a prospective open-label, individual randomised controlled clinical trial with 28 days blinded follow-up conducted in Vitongoji (VT) hospital and Mnazi Mmoja Hospital (MMH) in Zanzibar. Neonates at risk of early onset sepsis, admitted neonates (0-28 days) with clinical signs of sepsis and admitted children (6 months to 12 years) with febrile illness or diarrhoea that are eligible for participation and parents will be asked for informed consent. If informed consent is obtained the child will undergo randomization to intervention: CRP POCT measurement at 18-24 hours of life (at risk of early onset sepsis neonates) or CRP POCT at admittance and after 18-24 hours of treatment. Further treatment and discontinuation of antibiotics will be guided by flowcharts supporting the clinicians decision of treatment, please refer to description of intervention for further details. Participants will be randomly assigned (1:1) to either CRP-guided or standard-of-care antibiotic continuation/discontinuation. Both groups will be followed up by telephone up to 28 days after intervention. The principal investigator will not be aware of the results of the randomisation and follow-up will be blinded as well. CRP-level and treatment data will be recorded and entered in a central database.

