#### **Intervention**

CRP POCT equipment will be supplied at the two hospitals MMH and VT hospital, along with a training in use and interpretation supporting the clinical evaluation of the neonate and child.

- a) All included neonates delivered at one of the two hospitals with a risk factor of early onset sepsis as defined by WHO will have a CRP POCT measured at 18-24 hours of life. A measurement below 30mg/L indicates that the neonate does not need antibiotic treatment, CRP levels between 30mg/L and 50mg/L indicate caution and that the neonate should be

assessed clinically and CRP measurement repeated after 6 hours. CRP levels above 50mg/L indicate that the neonate needs antibiotic treatment for early onset sepsis, figure 1.

- b) For neonates admitted with suspected sepsis and randomized to the CRP group, antibiotic treatment should be initiated regardless of CRP levels and if possible including a blood culture. CRP will be reassessed after 18-24 hours of treatment, if both CRPs are below 10mg/L antibiotics are most likely not needed. The treatment is continued until the result of the blood culture, if negative the clinician can consider differential diagnosis and discontinuing the antibiotic treatment if the neonate is well. CRP levels above 100mg/L indicates severe disease and that the clinician should take into consideration meningitis and performing a lumbar puncture, figure 2.

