- c) For children 6 months to 12 years admitted with fever, history of fever or diarrhoea and in the intervention group, CRP will be taken at admittance and again at 18-24 hours. It will be communicated that if both CRP levels are less than 10mg/L it indicates that the disease is not severe, and antibiotics are most likely not needed and hence can be either not started or discontinued. If the second CRP is between 10mg/L and 50mg/L, antibiotics might be needed depending on whether the trend of the CRP is upwards or downwards. Hence, if antibiotics have been initiated the clinician can consider stopping the antibiotics earlier. If any of the CRP's are more than 50mg/L that it is likely that antibiotics are needed and treatment should be continued, figure 3. At all times the health care workers are instructed to take the clinical picture into account together with the value of the test. With obvious symptoms of bacterial infection with affected general condition, antibiotic treatment may be initiated and continued on clinical indication. The training of health care workers will also include knowledge of CRP pharmacodynamics and cases where a low CRP might need to be interpreted cautiously, e.g. a history of fever lasting less than 24 hrs. HCWs will be instructed to use CRP POCT for all patients in the intervention group and use the information to guide diagnosis and treatment choice. We will use an appropriate machine procured through the Ministry of Health, for instance Aidian QuickRead go CRP POCT set-up. Feasibility of using the CRP POCT will be assessed using the framework provided by Bowen et al describing acceptability, demand, implementation, practicality, adaptation, integration, expansion, limited-efficacy testing (4).

[figure not shown]

Aidian CRP POCT.

The training of HCWs will include the following flowcharts, figure 1 to 3

[figure not shown]

Figure 1: CRP intervention flowchart for neonates with risk factors of early onset sepsis (EOS)

[figure not shown]

Figure 2: CRP intervention flowchart for neonates with signs of infection

[figure not shown]

Figure 3: CRP intervention flowchart for children with febrile illness or diarrhea

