### **Sample size calculation**

For the superiority primary outcome, the sample size calculation is based on an estimated 20% reduction in duration of antibiotic treatment. Assuming the mean duration of antibiotic treatment of 7 days (168 hours) and an SD of 5 days (120 hours), with an  $\alpha$  of 0.05 and a  $\beta$  of 0.1. The trial needs 262 patients in each group (524 patients in total). However, some patients may be discharged before reaching the stopping rules and these patients would not be stopped according to the CRP guidelines. We assume that 20% of patients are going to be discharged before the stopping rule was enacted or lost to follow-up. To ensure enough power for independent analysis for the three study population groups we apply this power calculation for each group. Furthermore, for children 6 months to 12 years further inflation of sample size by 50% is done to ensure exploration of sub-groups with different symptoms of infection (e.g. pneumonia, diarrhoea etc.). To establish non-inferiority of the second primary outcome of relapse of infection, assuming event rate

of 5% of relapse, non-inferiority margin of 6%, one-sided alpha of 2.5%, power of 90% the sample size is 278 per group i.e. total 556 children plus 20% loss to follow-up equaling 646 children.

Hence, the study aims to include 646 neonates at risk of infection, 646 neonates with suspected infection and 969 children aged 6 months to 12 years with infection - an overall total of 2261 children included. Power calculations were performed using sample size calculators provided by Sealed Envelope (21).

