### **Randomisation and blinding**

We plan not to use the cluster randomization because it is not possible in the Zanzibar setting due to the limited number of sites (two) while cluster randomization requires a large number of sites that are relatively comparable. Furthermore, the current study in Kirgizstan has shown that individual randomization is feasible and can be applicable in Zanzibar (22). The randomisation will be carried out by a responsible Research Assistant through the Sealed Envelope™ programme ([www.sealedenvelope.com](http://www.sealedenvelope.com)). This person will inform the HCW directly of the result of the randomization. Follow-up will be blinded as well. Participants will be randomised (1:1) to either standard care or care according to CRP POCT. Randomisation will be stratified by male/female as well as within the three study groups.

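### The safety co-primary cannot register infection that follows withholding of antibiotics, which biases the non-inferiority test in at-risk neonates and, so far as antibiotics are never started, in older children

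*Protocol*

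**What the plan says.** The Study endpoints section introduces the outcome as a safeguard, "To ensure patient safety in case of reduction in antibiotic use a second primary outcome", and defines it in one clause: "relapse of infection is measured as reinstitution of antibiotics within 72 h after completion of the initial course of antibiotic treatment". Clinical signs of sepsis, readmission within 14 days and mortality at days 7 and 28 are secondary outcomes (items 5, 8 and 9).

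The Intervention section sets out three populations, called groups (a), (b) and (c) here after its items:

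- **Group (a), newborns at risk of early-onset sepsis:** "A measurement below 30mg/L indicates that the neonate does not need antibiotic treatment". Data analysis describes the comparator as two-day prophylaxis.
- **Group (b), neonates admitted with suspected sepsis:** antibiotics are started whatever the CRP.
- **Group (c), children 6 months to 12 years:** if both CRP values are low, "antibiotics are most likely not needed and hence can be either not started or discontinued".

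Specific objective 2a is to assess the safety as well as the effectiveness of CRP in guiding the start of treatment in group (a). The three groups are powered and analysed separately. Data analysis specifies intention-to-treat, with per-protocol as secondary and also used for a non-inferiority comparison in group (a).

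**The concern.** The event presupposes a course of antibiotics that was begun and finished. In group (a), and in part of group (c), the CRP strategy reduces antibiotic use by not beginning one. If a withheld newborn becomes septic and is first treated on day 3, that treatment is the initial course. It is not a reinstitution, and the failure is not counted.

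The main hazard of withholding is therefore invisible to the powered test meant to guard against it. The loss is also uneven between arms: it falls mostly on the CRP arm, because controls in group (a) are described as receiving prophylaxis. A non-inferiority result there would not answer objective 2a.

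A smaller gap affects both arms: a child who dies without a prior qualifying restart is not counted.

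**Working it through.** **Who can contribute an event**

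| Group | Initial course, CRP arm | Initial course, control arm | Failure after withholding counted? |
|---|---|---|---|
| (a) | None if CRP is low and the guidance is followed | Two-day prophylaxis | No |
| (b) | Every child | Usual care for suspected sepsis | Nothing is withheld at the start |
| (c) | Not started, or started and then stopped | Usual care, may also be untreated | No if never started; yes if started, stopped and restarted within 72 h |

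The protocol does not say how never-treated children are scored. Under intention-to-treat the natural reading is that they are non-events in the denominator. The per-protocol set keeps them as well, since withholding on a low reading is adherence. Excluding them would select on something the intervention determines. No route captures the missed failures.

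**The plan's own figure.** The Sample size calculation gives "of 5% of relapse, non-inferiority margin of 6%, one-sided alpha of 2.5%, power of 90% the sample size is 278 per group". With unpooled variance:

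n = (1.960 + 1.282)² × 2 × 0.05 × 0.95 / 0.06² = 10.507 × 0.095 / 0.0036 = 277.3, so 278 per arm. It reproduces.

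**Effect of uncounted failures.** Inputs:

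- From the protocol: control rate 5%, margin 6 percentage points, one-sided alpha 2.5%, 1:1 allocation, planned total 646 in groups (a) and (b).
- Per-arm size: 646/2 = 323; with 20% lost, 0.8 × 323 = 258.
- Assumed: a share w of the CRP arm is never started (the protocol gives no figure); all controls are treated; the true CRP-arm failure rate is 11% in treated and withheld children alike, exactly 5% plus the margin.

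Counted CRP-arm rate: c = (1 − w) × 0.11.

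SE = √[0.05 × 0.95/n + c(1 − c)/n].

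P(declare non-inferiority) = Φ[(0.06 − (c − 0.05))/SE − 1.96].

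Example, w = 30%, n = 258: c = 0.077. SE = √[(0.0475 + 0.0711)/258] = 0.0214. (0.06 − 0.027)/0.0214 − 1.96 = −0.42, and Φ(−0.42) = 0.34.

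| w | Counted rate | n = 258 | n = 323 |
|---|---|---|---|
| 0% | 11.0% | 2.5% | 2.5% |
| 5% | 10.45% | 4.2% | 4.5% |
| 10% | 9.9% | 6.9% | 7.7% |
| 30% | 7.7% | 34% | 41% |
| 50% | 5.5% | 80% | 88% |

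Every entry should be 2.5%. Simulation of this type of test at 278 per arm agreed with the formula within about one percentage point. Group (c) is planned at 969, about 484 per arm; at any w above zero the smaller SE makes the figures larger there.

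**Two variations**

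- *Controls also untreated.* With 30% untreated in both arms, the counted rates are 0.7 × 5% = 3.5% and 0.7 × 11% = 7.7%, a difference of 4.2 points. False non-inferiority is 14% (n = 258) to 17% (n = 323).
- *Harm confined to withheld children.* Take w = 50%, 5% relapse among those started and 17% failure among those withheld. The true rate is 0.5 × 5% + 0.5 × 17% = 11%, but the counted rate is 2.5%. At 278 per arm non-inferiority is declared in over 99.9% of trials, against 2.5% if all failures counted.

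**The case against.** A reader might infer that non-inferiority is guaranteed across the trial. The documents do not support that.

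- **Group (b) is outside the argument.** All its children start antibiotics, so nothing is withheld at the start.
- **Group (c) is affected only in part.** Its stated objective is discontinuation, and Study design and Study procedures place the second CRP after 18-24 hours of treatment. Children started and then stopped can have an event. How many are never started is unknown.
- **The test can still fail.** With half the CRP arm withheld and 20% relapse among those started, the counted rate is 10% against 5%, and non-inferiority is declared in only 6.5% of trials at 278 per arm.
- **It is too strong to say that withheld children, or children who die, can never be events.** A child treated late may finish that course and restart within 72 h. A child who restarts within 72 h and then dies is counted. Missed deaths occur in both arms, and no direction of bias from them has been shown.
- **The 72-hour window is not in itself a defect.** It has the same length in both arms, and counting from the end of treatment is a natural definition of relapse for a stopping strategy.
- **The harms are observed.** Sepsis signs, readmission and death are secondary outcomes, and a safety board reviews serious adverse events.

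All of this stands and limits the scope. It does not remove the defect in group (a). The secondary outcomes and board review are not the powered non-inferiority test, and the extra non-inferiority analysis in that group uses whether an antibiotic was prescribed, which does not measure harm. Nor is this a detail left to the analysis plan, because the protocol itself fixes the event definition.

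**Conclusion.** The concern holds for group (a), and for group (c) to the extent that antibiotics are never started. There the safety co-primary misses infection after withholding, and the bias runs towards non-inferiority. For group (a) the outcome does not answer objective 2a.

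The size depends on the withheld share, which the protocol does not give. At a true difference equal to the margin and with all controls treated, the false non-inferiority rate runs from the nominal 2.5% at w = 0 to 80-88% at w = 50%. The all-treated assumption fits group (a) best; untreated controls in group (c) reduce the bias. The equal 11% in treated and withheld children is also an assumption, and the bias grows if failures concentrate in those withheld.

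Non-inferiority is favoured in these groups, not guaranteed. The definition should be changed before a non-inferiority result is read as evidence that withholding is safe.

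**What to change.** For groups (a) and (c), and preferably all three for consistency, define the second primary as treatment failure over one fixed window from randomisation, with the same criteria in both arms. Count any of:

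- antibiotics started or restarted for new or worsening clinical infection after the initial treatment decision, excluding starts made at the scheduled initial decision or CRP reading;
- clinical signs of sepsis arising after that decision;
- readmission for infection;
- death.

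The first item must be arm-neutral. A criterion such as a first start after a recorded decision to withhold would arise almost only in the CRP arm, because group (a) controls are described as receiving prophylaxis. State how never-treated children and deaths are scored, and keep 72-hour reinstitution as a secondary outcome.

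Choose the window to fit the daily case report forms and the day 7 and day 28 contacts; Study design already provides that "Both groups will be followed up by telephone up to 28 days after intervention".

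The cost is one endpoint amendment, largely from data already planned. The 5% event rate and the stated power must be re-stated. At a fixed margin the required size scales with p(1 − p), so a higher rate under the broader definition means more children or less power. Part of the window will rest on caregiver recall, and restart decisions are made by clinicians in an open-label trial.

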### **Sample size calculation**

For the superiority primary outcome, the sample size calculation is based on an estimated 20% reduction in duration of antibiotic treatment. Assuming the mean duration of antibiotic treatment of 7 days (168 hours) and an SD of 5 days (120 hours), with an  $\alpha$  of 0.05 and a  $\beta$  of 0.1. The trial needs 262 patients in each group (524 patients in total). However, some patients may be discharged before reaching the stopping rules and these patients would not be stopped according to the CRP guidelines. We assume that 20% of patients are going to be discharged before the stopping rule was enacted or lost to follow-up. To ensure enough power for independent analysis for the three study population groups we apply this power calculation for each group. Furthermore, for children 6 months to 12 years further inflation of sample size by 50% is done to ensure exploration of sub-groups with different symptoms of infection (e.g. pneumonia, diarrhoea etc.). To establish non-inferiority of the second primary outcome of relapse of infection, assuming event rate

of 5% of relapse, non-inferiority margin of 6%, one-sided alpha of 2.5%, power of 90% the sample size is 278 per group i.e. total 556 children plus 20% loss to follow-up equaling 646 children.

Hence, the study aims to include 646 neonates at risk of infection, 646 neonates with suspected infection and 969 children aged 6 months to 12 years with infection - an overall total of 2261 children included. Power calculations were performed using sample size calculators provided by Sealed Envelope (21).

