Appendix 2.6: Clinical data registry

Appendix 2.7: Discharge form

Appendix 2.8: Follow-up form

Appendix 2.9: Health worker education and acceptability form

## **Data analysis**

Data analysis will include comparing baseline variables between the intervention and control groups using X tests for categorical variables and t-tests for continuous variables, without adjustment. Baseline characteristics such as age, sex, urban/rural residence, number of children, and study site will be compared. Separate analyses will be conducted for all three sub-groups neonates at risk of infection, neonates with signs of infection and children aged 6 months to 12 years.

The primary outcome duration of antibiotic treatment (days), which is a continuous variable, will be compared between the intervention and control groups using a multivariable linear regression model. Neonates at risk of early onset sepsis are recommended for two days of antibiotic treatment by the WHO. Therefore, in this subgroup, an additional non-inferiority analysis will be conducted using a multivariable logistic regression model, comparing CRP POCT with prophylactic two-day antibiotic treatment on the binary outcome of antibiotic prescribed yes/no. All comparisons will be conducted using both unadjusted and adjusted models for sex, age, and clinical status, following an intention-to-treat (ITT) approach. To account for deviations from CRP-based recommendations, a secondary Per-Protocol (PP) analysis will be conducted, excluding participants who did not adhere to their assigned intervention. For neonates at risk of early-onset sepsis, a non-inferiority comparison will be performed per protocol, assessing whether CRP-guided management is not inferior to standard clinical decision-making. Adherence to CRP-based recommendations will be systematically recorded and analyzed to evaluate its impact on treatment decisions. Statistical analyses will be performed after entering data from the final follow-up and data will be stored in a REDCap database for analysis using STATA.

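### Children discharged before the CRP stopping rule are counted as dropouts in the sample size, but ITT keeps them; in neonates with suspected sepsis, superiority power is about 81–89%, depending on an unstated split

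*Protocol*

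**What the plan says.** All design inputs are in the protocol's Sample size calculation. For superiority on antibiotic duration, "the sample size calculation is based on an estimated 20% reduction in duration of antibiotic treatment". The inputs are given as "Assuming the mean duration of antibiotic treatment of 7 days (168 hours) and an SD of 5 days (120 hours". The error rates are set at 5% (α) and 10% (β), and the result is stated as "The trial needs 262 patients in each group (524 patients in total".

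The section then notes that "some patients may be discharged before reaching the stopping rules and these patients would not be stopped according to the CRP guidelines", and continues: "We assume that 20% of patients are going to be discharged before the stopping rule was enacted or lost to follow-up". The calculation is applied to each of the three populations separately. The 20% appears again only as an addition to the headcount, where it is called loss to follow-up. The targets are "646 neonates at risk of infection, 646 neonates with suspected infection and 969 children aged 6 months to 12 years".

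Three other sections decide what happens to a child discharged early:
- Study endpoints measures duration over 14 days from admittance, so the window does not close at discharge.
- Follow-up by phone collects medicines taken after discharge, at day 7 and day 28.
- Data analysis makes the comparisons "following an intention-to-treat (ITT) approach", with per-protocol as a secondary analysis.

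No section removes early-discharged children from the primary analysis or lowers the assumed effect on their account.

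**The concern.** Two different problems share one allowance. A child lost to follow-up has no outcome, and recruiting more children makes up for that. A child discharged before the stopping rule normally does have an outcome and stays in the ITT analysis, but the protocol itself says that CRP does not stop that child's antibiotics. Such children pull the average difference between arms towards zero. If a fraction f of those analysed is unaffected, the ITT difference is (1 − f) × 1.4 days, and the required size grows by 1/(1 − f)². At f = 20% the factor is 1.56, where the plan uses about 1.2.

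At stake is whether the stated β of 0.1 describes the planned primary analysis. A null result in neonates with suspected sepsis would be read against 90% power that the design may not have.

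**Working it through.** **Inputs from the protocol.** Control mean 7 days; effect 20% × 7 = 1.4 days; SD 5 days; α 0.05; β 0.1; 1:1 allocation; 646 per neonatal group (323 per arm); 969 older children (484.5 per arm); 20% early discharge or loss combined.

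**Assumptions not in the protocol.** Two-sided α (not stated, but the only reading that comes near 262); zero effect and the same SD in early-discharged children; the split of the 20%, shown as a range.

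**Reproducing the plan's figure.** n per arm = 2 × 5² × (1.960 + 1.282)² / 1.4² = 50 × 10.507 / 1.96 = 268.04, rounded up to 269. The protocol has 262, which is within 3% and gives 89.3% power. A one-sided test would need 219, which does not match.

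**Power under the planned analysis.** Let e be the early-discharged share and l the lost share of those randomised, with e + l = 0.20.
- Analysed per arm: n = 323 × (1 − l)
- Unaffected share of those analysed: f = e / (1 − l)
- ITT effect: δ = 1.4 × (1 − f)
- Power = Φ( δ / (5 × √(2/n)) − 1.96 )

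| Early / lost | n per arm | δ (days) | Power |
|---|---|---|---|
| 20% / 0% | 323.0 | 1.120 | 81.2% |
| 15% / 5% | 306.8 | 1.179 | 83.2% |
| 10% / 10% | 290.7 | 1.244 | 85.1% |
| 5% / 15% | 274.6 | 1.318 | 87.0% |
| 0% / 20% | 258.4 | 1.400 | 88.9% |

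Worked example, first row: 5 × √(2/323) = 0.3934; 1.12 / 0.3934 = 2.847; 2.847 − 1.96 = 0.887; Φ(0.887) = 81.2%. In the 10%/10% row, early discharges are 0.10/0.90 = 11.1% of those analysed, which is why δ is 1.244 and not 1.26. The noncentral t distribution gives 81.1% to 88.8% across the same range.

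**Separating the two causes.** With no loss and no early discharge, 323 per arm gives 94.5%. Losing 20% costs 5.6 points (to 88.9%). Keeping 20% with no effect costs 13.3 points (to 81.2%). The same 20% is therefore much more expensive as early discharge than as loss.

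**Sensitivity to the zero-effect assumption.** If all 20% were early discharges who kept half the effect, δ = 0.8 × 1.4 + 0.2 × 0.7 = 1.26. Then 1.26 / 0.3934 − 1.96 = 1.243, and power is 89.3%.

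**Older children.** With 484.5 per arm the same formulas give 93.7% (20%/0%) to 97.4% (0%/20%).

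**The case against.** The strongest objection is that 1.4 days may already be the average over everyone randomised, in which case nothing is diluted. The text does not say so, and a separate allowance for early discharge would then have no purpose. It is still a legitimate way to settle the point, provided that it is stated.

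Zero effect is also an assumption. The protocol says that these children are not stopped by CRP, not that CRP leaves their treatment unchanged. An admission CRP is taken as well, and under Intervention a low value in an older child can mean that antibiotics are never started. This stands: the 81.2% is a lower bound under a stated assumption.

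Some early-discharged children may have no usable duration, because post-discharge data come from calls or home visits. They would then act as true losses, which moves the result towards the 88.9% end but not outside the range.

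As written, 646 is derived from the non-inferiority calculation, so the protocol does not literally claim 90% superiority power at 646. That is fair. However, the superiority β is 0.1, the 20% allowance is introduced in that calculation, and the section says that it applies to each group. (Separately, 556 plus 20% is 667, not 646; 646 equals 2 × 269 × 1.2.)

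A reader might infer that 81–89% holds equally for both neonatal groups. The documents do not support that. For neonates at risk of early onset sepsis, Specific objectives and Intervention use CRP to guide whether antibiotics are started, and Data analysis refers to a two-day recommended course. A 7-day mean, SD of 5 and discharge before a stopping rule do not describe that group.

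**Conclusion.** The point holds for neonates with suspected sepsis. The protocol handles early discharge as missing data, while its primary analysis keeps these children, for whom by its own account the CRP stop does not happen. Superiority power at 646 is about 81% to 89%, depending on a split that the protocol does not give, if early-discharged children have zero effect and the same SD and if 1.4 days is the effect in children who reach the stopping rule.

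Four stronger readings should be resisted:
- The whole range is not caused by dilution. The 88.9% end contains no early discharge and is practically the planned 90%.
- 81% is not the expected power. It requires that all of the 20% are early discharges.
- The older children are not short of power, although their extra 50% was meant for exploring subgroups.
- Dilution would also make the arms more alike on relapse, which tends to favour non-inferiority. That is a direction only; the documents give no basis for a size.

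The mechanism is certain; the size is not. This is a correction to a stated property of the design, not a reason to doubt that the trial can answer its question.

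**What to change.** In the Sample size calculation:

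1. Split the 20% into loss to follow-up and discharge before the stopping rule, with a basis for each.
2. Use headcount inflation for loss only, and apply early discharge as a reduction of the assumed ITT effect.
3. For neonates with suspected sepsis, restate superiority power at 646 as about 81–89% depending on the split, and name the zero-effect and equal-SD assumptions. Alternatively, state explicitly that 1.4 days is the average effect over all randomised children.
4. Restate no power figure for neonates at risk of early onset sepsis on this basis. The 7-day, SD 5 inputs and the two-day course cited in Data analysis must first be reconciled.

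The trial need not be enlarged. Full 90% power with 20% early discharges retained would take 50 × 10.507 / 1.12² = 418.8, so 419 per arm (838 in the group), which is out of proportion to the problem. The cost is a text change and a less favourable stated power; recruitment, conduct and analysis are unaffected.

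### At-risk neonates: the 90% power for antibiotic duration is computed from a 7-day course, but the protocol gives this group a two-day comparator, so the power for duration is undetermined

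*Protocol*

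**What the plan says.** The Protocol's Study endpoints section defines one primary effectiveness outcome for all participants: "The primary study outcome is the duration of antibiotic treatment (number in 24-hour periods between start and end of antibiotic treatment"), counted within 14 days of admittance and tested for superiority.

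The Sample size calculation section gives a single calculation for it. The effect is set first: "the sample size calculation is based on an estimated 20% reduction in duration of antibiotic treatment". The distribution follows: "Assuming the mean duration of antibiotic treatment of 7 days (168 hours) and an SD of 5 days (120 hours"), with α 0.05 and β 0.1. The result is: "The trial needs 262 patients in each group (524 patients in total"). The section then extends this to every population: "To ensure enough power for independent analysis for the three study population groups we apply this power calculation for each group".

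The Data analysis section confirms that the populations stand alone: "Separate analyses will be conducted for all three sub-groups neonates at risk of infection, neonates with signs of infection and children". For one of them it gives a different course length: "Neonates at risk of early onset sepsis are recommended for two days of antibiotic treatment by the WHO". For that reason it adds an analysis in this group "comparing CRP POCT with prophylactic two-day antibiotic treatment on the binary outcome of antibiotic prescribed yes/no". Duration remains this group's primary superiority outcome. The protocol states no mean, SD or target difference specific to it.

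**The concern.** The sample size inputs describe patients on roughly a week of treatment whose course might be shortened. The at-risk neonates are a different case. By the protocol's own account their comparator is a two-day prophylactic course, and the Intervention section uses CRP in this group mainly to decide whether antibiotics are needed at all. The mean, the SD and the absolute difference in the calculation therefore have no evident connection to this group.

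The group is one of three to be analysed independently, with 646 neonates planned. If its duration result is null, a reader will want to know what difference the trial could have detected. The protocol's answer, 1.4 days with 90% power, comes from figures that its own Data analysis section contradicts for this group.

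**Working it through.** **Inputs from the protocol.** Control mean 7 days, SD 5 days, reduction 20%, α 0.05 (taken as two-sided, which fits the stated size), power 90%, allocation 1:1. Course in at-risk neonates: 2 days. Planned size of that group: 646, or 323 per arm. After the assumed 20% loss or early discharge, 323 × 0.8 ≈ 258 per arm. Early-discharged neonates may still be analysed by intention to treat, so 258 is the lower end and 323 the upper.

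**Reproducing the plan's figure.** n per arm = 2 × [SD × (1.96 + 1.2816) / δ]².

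- δ = 0.20 × 7 = 1.4 days, SD = 5: n = 2 × (5 × 3.2416 / 1.4)² ≈ 268.05, so 269.
- δ rounded to 34 hours, SD = 120 hours: n = 262, the stated figure.

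The calculation is sound for its own inputs.

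**Moving it to a two-day course.** 20% of 2 days is 0.4 days. Keeping 1.4 days would mean 1.4 / 2 = 70%. The relative and the absolute targets no longer agree.

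**What power follows.** Power = Φ(δ / (SD × √(2/n)) − 1.96) with δ = 0.4. The detectable difference at 90% power is SD × √(2/n) × 3.2416. At n = 258, √(2/258) = 0.0880. The SDs are assumed; 1.43 is 2 × 5/7, the same SD-to-mean ratio as in the plan.

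| Assumed SD (days) | Power for 0.4 d, 258/arm | Power for 0.4 d, 323/arm | n per arm for 90% | Detectable at 90%, 258/arm |
|---|---|---|---|---|
| 1 | 99.5% | 99.9% | 132 | 0.29 d |
| 1.43 | 89% | 94% | 269 | 0.41 d |
| 2 | 62% | 72% | 526 | 0.57 d |
| 3 | 33% | 40% | 1183 | 0.86 d |

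At 258 per arm the SD must be about 1.40 days or less to give 90% power for 0.4 days.

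**Limits on the SD.** Duration within 14 days lies between 0 and 14, so with a mean of 2 the SD cannot exceed √(2 × 12) = 4.90. The plan's SD of 5 is therefore impossible at that mean and is left out of the table. At the other extreme, if every neonate received either 0 or 2 days, the SD would be 2√(p(1−p)), at most 1 day.

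**Larger effects.** If CRP guidance avoided the two-day course in half of the intervention arm (an assumed 1.0-day difference), power at 258 per arm would be 97% at SD 3 and about 100% at SD 2 or less.

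**The case against.** The strongest reply is that no shortfall has been shown, and that is right. If the SD shrinks in proportion to the mean, the required size stays at 269 per arm. If outcomes are mostly 0 or 2 days, the SD is at most about 1 day and power for 0.4 days exceeds 99%. Withholding treatment below a CRP threshold could also give a relative effect well above 20%. A reader might infer that the group is underpowered, but the protocol does not support that.

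Secondly, two days is a WHO recommendation and the named comparator of an additional analysis. Controls receive standard care, and no local duration is reported. The 0.4-day target is thus itself conditional. This limits the size of the point but does not restore the 7-day figure, which the protocol nowhere justifies for this group.

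Thirdly, a reader might infer that the group's whole sample size is without basis. That goes too far. The relapse outcome has its own inputs (5% event rate, 6% margin, one-sided 2.5%, 90% power), its 278 per arm reproduces, and the section attaches the figure of 646 to that calculation. Whether the loss-to-follow-up step there is correct is a separate matter.

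Finally, a reader might conclude that duration should give way to a yes/no outcome because the latter has more power. That does not follow. With durations of 0 or 2 days, duration is twice the yes/no indicator. For 95% versus 85% treated, the difference is 0.20 days, the standard error is √((0.19 + 0.51)/258) = 0.052, and power is 97%, the same as for the two proportions.

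**Conclusion.** Wrong as written, and it should be fixed. For at-risk neonates, the 90% power for duration rests on a mean, SD and absolute difference that the Data analysis section contradicts. Nothing else in the protocol supplies a basis, so power for duration in this group is undetermined. Across assumed SDs of 1 to 3 days, power for a 20% reduction of a two-day course runs from over 99% down to 33% at 258 per arm, and the difference detectable at 90% power from about 0.29 to 0.86 days.

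The conclusion rests on taking the two-day comparator as the control course. The range rests on SDs that the protocol does not give. The point is confined to duration in this one population: it is a missing basis for a stated power, not a demonstrated lack of power.

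**What to change.** In the Sample size calculation section, stop applying the 7-day, SD 5 calculation to at-risk neonates. Keeping the planned 646, state for that group:

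- a control mean consistent with the two-day comparator, or the observed local duration if it differs, with its source;
- an SD for that group;
- the resulting power for a named reduction, or the difference detectable with 90% power.

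Optionally, report a superiority comparison of any antibiotic started (yes/no) beside duration. The Data analysis section already plans to use that variable in this group, so no new data are needed. Replacing the primary outcome is not required.

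The cost is a change of text and a short calculation, with enrolment and data collection unchanged. The downside is that the stated power for this group may turn out less favourable than 90%.
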